## Methods and analysis

### Design, settings and population

We will conduct a cross-sectional survey among patients with a clinical diagnosis of SMI recruited at national specialist mental health institutions. In Bangladesh, the study will be conducted at the National Institute of Mental Health and Hospital (NIMHH) in Dhaka. NIMHH offers 200 beds for in-patient care and on average 400 outpatients attend every day. In India, the study will be conducted at the National Institute of Mental Health and Neurosciences (NIMHANS) in Bengaluru, with 650 beds for in-patient care; on average at NIMHANS, 400 outpatients attend every day. In Pakistan, the study will be conducted at the Institute of Psychiatry (IOP) Rawalpindi Medical University, a WHO collaborating centre for the Eastern Mediterranean. IOP offers 60 beds for inpatients and on average 400 outpatients attend every day. All three national institutes serve patients from all over the country. Adults (18 years and over) with a clinical diagnosis of SMI (defined by the International Classification of Disease 10th revision (ICD-10^23^) as schizophrenia, schizotypal and delusional disorders (F20-F29); bipolar affective disorder (F30, F31) and severe depression with psychotic symptoms (F32.3, F33.3)),^23^ who are able to provide informed consent as assessed by the treating clinician will be recruited. Patients who lack capacity to provide consent or are unable to complete study questionnaires will be excluded (figure 1). The data will be collected from June 2019 to September 2020.

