### Recruitment and random selection of the participants

Both inpatients and outpatients attending one of the three specialist mental health institutions collaborating in this study will be recruited. At NIMHH and NIMHANS, patients will be selected randomly using random number tables generated centrally to determine for outpatients, which patient to approach on a given day, and for inpatients by randomly selecting beds. Recruitment is separated by inpatients versus outpatients, resulting in a proportion of 80% outpatients and 20% inpatients (which has been reported as the ‘usual’ proportion of inpatients and outpatients). Due to the lower volume of patients and outpatients reaching the centre outside working hours at the IOP, all patients attending the IOP during the study duration will be invited to participate in the survey.

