### Statistical analysis

Quantitative data will be summarised using descriptive statistics. First, prevalence rates of infectious diseases, long-term physical health conditions (eg, diabetes, heart disease) and health-risk behaviours for type II diabetes, cardiovascular and respiratory disorders (eg, tobacco use, obesity, physical activity, diet) will be estimated in the SMI population. Second, we will examine the associations between physical health conditions and health-risk behaviours, using regression models with random intercepts for data collection site with the following potential covariates: demographic variables (ie, age, sex and level of education), history of mental and physical conditions and biomarkers (eg, body mass index, BP). These regression models will also be used to calculate prevalence rates of physical health conditions and health-risk behaviours adjusted for these covariates (eg, for comparison with external general population data). Further regression analyses will explore the association between mental and physical health conditions and health-related quality of life measured using EQ-5D-5L. Regression models will take account of the nature and distribution of data (eg, count vs continuous data; skewed vs normally distributed data). To investigate the prevalence of physical health conditions and health risk behaviours in the general population, we will extract aggregated data on the prevalence of physical health conditions, health risk behaviours and lifestyle advice from the last available WHO STEPS survey from Bangladesh,^44^ India^45^ and Pakistan.^46^

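### With three named sites, one per country, site should be a fixed effect: the planned random intercept weakens the adjusted prevalences but leaves the association estimates essentially intact

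*Protocol article*

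**What the plan says.** The Statistical analysis section of the protocol article first describes prevalence estimation. As a second step it turns to associations between conditions and behaviours, to be analysed "using regression models with random intercepts for data collection site with the following potential covariates". The next sentence gives the models a further use: "These regression models will also be used to calculate prevalence rates of physical health conditions and health-risk behaviours adjusted for these covariates", with comparison against external general-population data as the example.

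The number of sites is fixed elsewhere. Recruitment takes place at "one of the three specialist mental health institutions collaborating in this study". Under Design, settings and population there is one per country. For Bangladesh the text reads "In Bangladesh, the study will be conducted at the National Institute of Mental Health and Hospital (NIMHH) in Dhaka". For India it reads "In India, the study will be conducted at the National Institute of Mental Health and Neurosciences (NIMHANS) in Bengaluru". For Pakistan it names the Institute of Psychiatry in Rawalpindi. They are chosen national institutes, not a sample of sites.

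The Sample size section sets numbers and precision per country (1500 each; 857 needed for ±2 points at 10% prevalence). The comparators are three separate national STEPS surveys, and Strengths and limitations frames the comparison as one within each country.

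**The concern.** A random intercept treats the sites as draws from a normal population of sites and estimates the variance of that population. Three units give 2 degrees of freedom for it. Because each country has one site, the model also has no separate country parameter, although country is the level at which the study is sized and compared with the general population.

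What is at stake is any adjusted prevalence taken from these models, because it depends on the intercept. A pooled figure would describe an average site, with an interval built on a variance that can hardly be estimated. A country figure would be a prediction shrunk towards the other two countries. A slope, by contrast, is estimated almost wholly from contrasts within sites, so it should be much less exposed.

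**Working it through.** **Inputs from the article:** 3 sites, one per country; 1500 per site, 4500 in all; 10% prevalence; 95% intervals. **Assumed, because the article gives none:** between-site SD on the logit scale, 0.1 to 0.8; maximum likelihood (ML) or REML estimation; z-based intervals. I take data collection site to mean the institute, since no smaller unit is named.

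**1. The plan's own figure.** n = 1.96² × 0.1 × 0.9 / 0.02² = 864.3, so 865. The stated 857 is within 1% of this, and a finite-population correction with an assumed population of 100,000 gives 856.9. The figure is not in error, and it is a per-country figure. At n = 1500 the half-width is 1.96 × √(0.09/1500) = 0.0152, about ±1.5 points.

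**2. Precision of the between-site SD.** Even with the site effects known exactly, the limits as multiples of the estimate are √(2/χ²) on 2 df: √(2/7.378) = 0.52 and √(2/0.0506) = 6.28.

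**3. Coverage of a z-based pooled interval when between-site variance dominates.** For 2 df, P(|t| < x) = x/√(2 + x²).
- REML: x = 1.96 gives 1.96/2.417 = 81.1%.
- ML: x = 1.96 × √(2/3) = 1.600 gives 1.600/2.136 = 74.9%.
- The 2-df critical value is 4.30, not 1.96.

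**4. Simulation.** Random-intercept logistic model, ML by adaptive quadrature, Wald z intervals, 3 × 1500, about 10% prevalence, one binary covariate with log odds ratio 0.4, 400 runs per setting (Monte Carlo standard error 1–2 points).

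| Assumed SD | Pooled intercept coverage | Slope coverage, random site | Slope coverage, fixed site | Median estimated SD | SD estimated near zero |
|---|---|---|---|---|---|
| 0.1 | 89.5% | 94.8% | 94.8% | 0.03 | 47% |
| 0.3 | 78.8% | 97.0% | 97.0% | 0.20 | 12% |
| 0.5 | 73.3% | 96.8% | 97.0% | 0.31 | 7% |
| 0.8 | 75.5% | 93.3% | 93.3% | 0.55 | 2% |

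The intercept undercovers as inference about a population of sites. The slope does not, and its coverage hardly depends on the choice of site term. Across checks, pooled coverage at SD 0.1 was about 87–90%.

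**5. The same interval read as the mean of these three sites.** A further simulation (300 runs per setting, SD 0.2, 0.3 and 0.5) gave coverage of 98%, 99% and 99%, which is too wide. The reason shows in the arithmetic. The sampling variance of one site's logit is 1/(1500 × 0.09) = 0.0074, so the mean of three has standard error √(0.0074/3) = 0.050. Adding a between-site SD of 0.20 (the median estimate when the truth is 0.3) gives √((0.04 + 0.0074)/3) = 0.126, about 2.5 times as large.

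**6. Shrinkage of country predictions.** The weight on the common mean is 0.0074/(SD² + 0.0074):
- SD 0.1: 0.0074/0.0174 = 43%
- SD 0.2: 0.0074/0.0474 = 16%
- SD 0.3: 0.0074/0.0974 = 8%
- SD 0.5: 0.0074/0.2574 = 3%

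**The case against.** Three stronger readings are tempting, and the documents support none of them.

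- **That every pooled 95% interval from these models falls far short.** The sentence specifying the random intercept is about associations, and the slopes keep about nominal coverage either way. The shortfall is confined to quantities that depend on the intercept.
- **That a zero variance estimate removes the adjustment for country and lets country confound the associations.** The estimate collapses to zero mainly when observed site differences are about the size of sampling noise, which is when country can confound least. With exposure deliberately tied to the site effect, and SDs of 0.2, 0.3 and 0.5, zero estimates occurred in 21%, 11% and 4% of runs. The mean slope bias in those runs was only 0.03 to 0.04 on a log odds ratio of 0.4. Over all runs it was about 0.01, with slope coverage of 92–94%.
- **That the main prevalence results are compromised.** The article describes prevalence estimation as a first step, before the regressions. Unadjusted country prevalences need no between-site variance.

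It is also fair to say that the article nowhere commits to a pooled adjusted prevalence with a Wald interval. It names no estimator, interval method or small-sample correction, and these may be settled in an analysis plan that is not shown. The 73–81% therefore depends on choices the article leaves open. And if the three institutes are of interest in themselves, the error runs the other way, towards an interval that is too wide.

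What stands after all this is the stated model. The random intercept is fixed in the text, the adjusted prevalences come from it, and no stated objective needs generalisation to other sites.

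**Conclusion.** The point holds in a limited form. With three chosen sites, one per country, the between-site variance is not usefully estimable, and the random intercept does not match the per-country target of the study.

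The association estimates are essentially unaffected. The damage is to adjusted prevalences from the same models. A pooled interval has the wrong width: too narrow beyond these sites, too wide for the three sites themselves. Country predictions are shrunk, modestly at SD 0.2 or more; the larger shrinkage at SD 0.1 arises where the countries barely differ.

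The coverage sizes rest on an assumed between-site SD and on z-based intervals; the simulated slopes did not vary by site. This is an inexpensive improvement that should be made, not a condition for the analysis to stand.

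**What to change.** In the Statistical analysis section, replace the random intercept with country (site) as a three-level fixed effect in the regression models. State that covariate-adjusted prevalence will be reported separately by country and compared with that country's STEPS survey.

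The cost is one or two sentences and two degrees of freedom out of 4500. Slope coverage stays the same in the simulation. What is given up is a claim to generalise to other sites, which three sites cannot support.

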In South Asia, rates of mental illness and physical non-communicable diseases have been increasing rapidly.^13 14^ This increase, coupled with the lack of access to even basic mental healthcare,^15^ and neglect of the physical health needs of people with SMI by policymakers and healthcare services,^16^ means that the burden of disease due to physical disorders in people with mental illness. is set to rise further, with a corresponding increase within country and global health inequalities. This increase is coupled with a recognised lack of information about the prevalence of physical conditions and health risk behaviours in the SMI population in South Asia.^17^ This gap in knowledge, particularly in relation to health service planning in LMICs, has been pointed out repeatedly as a priority for research.^18^ Addressing mental and physical health comorbidity in LMICs is also a global priority, recognised in global policies to help achieve the sustainable development goals, including ‘ensuring healthy lives and promoting well-being for all’.^19–21^ A detailed understanding of the prevalence of physical health conditions, health risk behaviours and health service utilisation in SMI in LMICs is needed to progress this agenda.^22^

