### Objectives

In people with SMI attending specialist mental health facilities:

Determine the prevalence of physical health conditions (ie, type 2 diabetes, hypertension, heart disease, obesity and infectious diseases) and health-risk behaviours (ie, diet, physical activity, alcohol and tobacco use) and compare these findings with those reported in the general population.Determine the association between physical health conditions, health-risk behaviours, health-related quality of life and various demographic, behavioural, cognitive, psychological and social variables.Identify health-service utilisation and the type of lifestyle advice that has been offered for this population.Support clinical trial readiness by providing evidence-based findings regarding outcome measures and procedures relevant for clinical trial design.

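### SMI prevalence adjusted for BMI, blood pressure and disease history has no matching quantity in the aggregate STEPS data it is meant to be compared with

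*Protocol article*

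**What the plan says.** Objective 1 of the protocol article is to estimate the prevalence of physical conditions and health-risk behaviours in people with SMI and to "compare these findings with those reported in the general population". The conditions named are "type 2 diabetes, hypertension, heart disease, obesity and infectious diseases".

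The Statistical analysis section first plans descriptive prevalence. It then sets up regression models for the associations "with the following potential covariates: demographic variables (ie, age, sex and level of education") and, in the same list, "history of mental and physical conditions and biomarkers (eg, body mass index, BP"). The next sentence gives those models a second use: "These regression models will also be used to calculate prevalence rates of physical health conditions and health-risk behaviours adjusted for these covariates", with the purpose given as "eg, for comparison with external general population data".

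For the general population, the same section says "we will extract aggregated data on the prevalence of physical health conditions, health risk behaviours and lifestyle advice", taken from the latest STEPS survey in each country. The Strengths and limitations section confirms that the study has no control group. The abstract describes the comparison with STEPS without naming any adjustment.

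**The concern.** One covariate list serves two different purposes. For associations within the SMI sample, disease history, BMI and BP are reasonable candidates. For an external comparison, adjustment helps only if both sides can be brought to the same covariate distribution. With aggregated data on one side, that is possible only for variables by which the published tables are broken down.

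History, BMI and BP raise three further problems:

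- History of mental illness has no usable reference value in the general-population figures.
- BMI defines obesity and BP enters the definition of hypertension, and both are Objective 1 outcomes.
- For diabetes and heart disease, BMI and BP may lie on the path by which SMI raises risk, so holding them fixed can remove part of the excess that the study sets out to measure.

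At stake is the general-population half of Objective 1: an adjusted figure placed beside a STEPS figure may be read as a like-for-like excess when it is not.

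**Working it through.** **1. The statements side by side.** The adjusted SMI prevalence comes from models whose candidate covariates are age, sex, education, disease history, BMI and BP. Its stated use is external comparison. The comparator is aggregate prevalence. The section names no reference distribution and does not separate the comparison model from the association models.

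**2. Yardstick for size.** The Sample size section assumes 10% diabetes prevalence.

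- Its indicative calculation: n = 1.96² × 0.10 × 0.90 / 0.02² = 864.4, so 865. The article gives 857, about 0.9% lower, which is close enough; the point does not depend on it.
- Half-width at the planned 1500 per country: 1.96 × √(0.09/1500) = 1.52 points. The ±2 points belong to the 857 example.

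**3. BMI adjustment, diabetes (assumed inputs).** The documents give no covariate distributions, so these are assumptions: BMI normal with mean 23 and SD 4.5 in the general population; SMI mean 1 to 3 units higher with the same SD; odds ratio (OR) 1.05 to 1.15 per BMI unit. The model is logit(p) = a + ln(OR) × (BMI − 23), with a solved so that crude SMI prevalence is 10%. Three ways of producing the adjusted figure are possible, and the article does not say which applies.

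- *Averaged over the SMI sample's own BMI mix:* it returns about 10.0%, the crude figure. Nothing is distorted and nothing is adjusted.
- *Evaluated at the SMI sample's mean BMI:* 9.83%, 9.37% and 8.71% for OR 1.05, 1.10 and 1.15, a shift of 0.17 to 1.29 points. This value corresponds to no STEPS quantity.
- *Set to the general-population BMI distribution:*

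| SMI BMI excess | OR 1.05 | OR 1.10 | OR 1.15 |
|---|---|---|---|
| 1 unit | 9.57% | 9.19% | 8.85% |
| 2 units | 9.16% | 8.43% | 7.82% |
| 3 units | 8.76% | 7.74% | 6.89% |

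Under the third rule the shift from 10.0% is 0.43 to 3.11 points, and it exceeds 1.52 points in four of the nine cells (1.57, 2.18, 2.26 and 3.11). If SMI acts on diabetes only through BMI, the whole gap goes to zero. If there is also a direct SMI odds ratio of 1.3, the gap falls from 2.46 to 2.04 points in the mildest cell and from 4.58 to 1.47 in the strongest.

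**4. BMI adjustment, obesity.** With the same BMI assumptions, a 2-unit excess and a BMI cut-off of 30, the crude contrast is 13.3% against 6.0%. Setting BMI to the general-population distribution gives 6.0% against 6.0%. This follows by construction, because the covariate determines the outcome.

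**5. The crude route.** Assume identical age-specific risks of 3, 10 and 18%, an SMI age mix of 60/32/8 and a general-population mix of 55/27/18.

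- SMI: 0.60×3 + 0.32×10 + 0.08×18 = 6.44%.
- General population: 0.55×3 + 0.27×10 + 0.18×18 = 7.59%.

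A deficit of 1.15 points (15% in relative terms) appears with no true difference. This illustrates the limit of the unadjusted comparison. It says nothing against adjusting for age and sex.

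**The case against.** The text is permissive. The covariates are called potential, and both the biomarkers and the external comparison are introduced as examples. A full protocol or analysis plan, not shown here, may settle a narrower set. Descriptive prevalence comes first, and the abstract describes the STEPS comparison without adjustment, so a crude figure would be available beside any adjusted one. The large distortions in the working arise under one prediction rule that the article does not state; averaging over the sample's own BMI mix leaves the excess intact.

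Most of this stands, and it limits the point. A reader might infer that the main contrast of Objective 1 rests on the over-adjusted figure, or that adjustment will erase the SMI excess. The article supports neither: the adjusted figure is an additional output, and its effect could be nil. Nor does it follow that aggregate STEPS data can be matched on nothing, since published figures may be broken down by age and sex.

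What does not stand is that the matter is simply left to a later document. The article names the models, the covariate list and the use, and links them in one sentence. That is a stated method, and it suits the external comparison poorly. The crude figure does not rescue it, because it is not matched on age or sex.

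**Conclusion.** The point holds as a should-fix. As written, one route to the general-population comparison adjusts for variables that aggregate STEPS prevalence cannot match, and the other adjusts for nothing. Neither gives the SMI excess at equal age and sex.

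The documents do not allow the distortion to be sized. On the assumed BMI inputs, the shift in a 10% diabetes prevalence runs from zero to about 3.1 points, against a half-width of about 1.5 points at 1500 per country. It is negligible under some prediction rules and larger than sampling error under others. These figures cover BMI only; BP and disease history were not modelled. The circularity for obesity and hypertension needs no assumption about size: it applies whenever BMI or BP enters the model for its own outcome.

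**What to change.** Separate the two uses in the Statistical analysis section.

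- Keep history of mental and physical conditions, BMI and BP as candidate covariates for the association models only.
- For the external comparison, directly standardise SMI prevalence, country by country, to the age and sex distribution of that country's STEPS survey, using the strata its report publishes.
- Report the standardised figure beside the crude one, with an interval for the contrast that allows for STEPS sampling error where it is published.

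This assumes that the STEPS reports give age-by-sex breakdowns, which the article does not show. Age and sex are already collected through the STEPS demographic module, so the change is one of wording plus a weighting step.

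The cost is some precision, and participants outside the STEPS age range drop out of this one comparison. On the assumed age mix in step 5 of the working, with n = 1500, the crude half-width is 1.96 × √(0.0644 × 0.9356/1500) = 1.24 points. The standardised half-width is 1.96 × √[(0.55²×0.03×0.97/0.60 + 0.27²×0.10×0.90/0.32 + 0.18²×0.18×0.82/0.08)/1500] = 1.96 × √(0.0950/1500) = 1.56 points. The loss is about 0.3 points in that example and smaller where the age mixes are closer.

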### Strengths and limitations

To the best of the authors’ knowledge, this will be the first large-scale study to investigate the physical health and health-risk behaviours in the SMI population in LMICs. The main limitation is that the survey is conducted in specialist centres (with patients with capacity) and is therefore a healthcare utilisation sample drawn largely from tertiary care. The gaps in treatment and care utilisation and systematic factors influencing these have been well documented,^50^ therefore, the study population may not be representative of the total SMI population in each country. However, a community survey would not be feasible, and primary and secondary care mental health services are not sufficiently developed to be used to recruit participants for this survey (see, eg, work by PRIME^15^ and Emerald^51^ programmes on strengthening these services as access points). However, unlike services in HICs, tertiary care services in these South Asian countries accept self-referral without the need for primary or secondary care referral and we include outpatient services offered by the collaborating centres which often function as ‘the first port of call’ for people with mental illness.^52–54^ Therefore, the selected centres are likely covering a broad range of the treatment-seeking population. We will not have a control group since the study is only conducted in people with SMI, however we are using the same questions and measurements as the WHO STEPS survey. This will allow us to compare the prevalence of physical health conditions and health risk behaviours with that of a survey representative for the population in each country.

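### For non-communicable diseases, the comparison with each country's last STEPS survey mixes SMI status with calendar time and could inflate the apparent SMI excess; the size cannot be fixed from the protocol

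*Protocol article*

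**What the plan says.** Objectives: after estimating prevalence in the SMI sample, the first objective is to "compare these findings with those reported in the general population".

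Design, settings and population: "The data will be collected from June 2019 to September 2020".

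Statistical analysis: for the general population, "we will extract aggregated data on the prevalence of physical health conditions", on health-risk behaviours and on "lifestyle advice from the last available WHO STEPS survey from Bangladesh", with India and Pakistan following. One survey is cited per country. The regression models are also to supply adjusted prevalences for the external comparison. Their potential covariates are "demographic variables (ie, age, sex and level of education), history of mental and physical conditions and biomarkers". Calendar time is not among them.

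Background: in South Asia, "rates of mental illness and physical non-communicable diseases have been increasing rapidly". No annual rate is given.

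Strengths and limitations, in the Discussion: the protocol acknowledges that there is no control group and answers that "we are using the same questions and measurements as the WHO STEPS survey". It continues: "This will allow us to compare the prevalence of physical health conditions and health risk behaviours with that of a survey representative for the population" of each country. Survey date appears neither there nor in the bulleted limitations after the abstract.

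**The concern.** The two sides of the comparison differ in SMI status and also in when they were measured. If the prevalence of a disease rises between the STEPS fieldwork and 2019-2020, the SMI sample will show a higher figure even if SMI has no effect. The protocol itself says that non-communicable diseases are rising rapidly, so for them the tilt is towards an excess in SMI. That is also the direction the Background leads readers to expect.

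Neither of the plan's safeguards reaches this. Shared instruments remove differences in measurement, and a representative survey removes some differences in selection; neither aligns dates. The adjustment models are fitted to SMI participants only, because the comparator is available only in aggregate. They can standardise the SMI figures for age, sex and education, but they hold no information on how the general population changed between the two surveys.

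At stake is the reading of a first-objective result: how much of an observed difference in diabetes, hypertension, heart disease or obesity can be attributed to SMI.

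**Working it through.** **The plan's own figure.** Sample size assumes 10% diabetes prevalence, ±2 points and a 95% CI, and states 857 per country.

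n = 1.96² × 0.10 × 0.90 / 0.02² = 864.3, so 865.

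The stated 857 is 8 lower (0.9%), which is close enough to count as reproduced; a finite-population correction with an assumed population of 100,000 gives 856.9. This figure is not in question. It supplies the 10% used below.

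**Half-width at the planned size.** With n = 1500 per country:

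1.96 × √(0.10 × 0.90 / 1500) = 0.0152, or 1.52 percentage points.

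**Drift with no true SMI effect.** Let prevalence be 10% in both populations in 2019-2020. Let g be the relative rise per year and y the years since the STEPS fieldwork. Both are assumptions; the protocol text gives neither.

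- STEPS prevalence: p0 = 0.10 / (1 + g)^y
- Spurious excess: b = 0.10 − p0

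Example, g = 3% and y = 5: p0 = 0.10 / 1.03⁵ = 0.0863, so b = 1.4 points.

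| Spurious excess (points) | g = 1% | g = 2% | g = 3% | g = 5% |
|---|---|---|---|---|
| y = 1 | 0.1 | 0.2 | 0.3 | 0.5 |
| y = 2 | 0.2 | 0.4 | 0.6 | 0.9 |
| y = 5 | 0.5 | 0.9 | 1.4 | 2.2 |
| y = 10 | 1.0 | 1.8 | 2.6 | 3.9 |

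The corresponding prevalence ratios run from 1.01 to 1.63.

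**Break-even.** Drift equals the half-width when (1 + g)^y = 0.10 / (0.10 − 0.0152) = 1.179. That needs g = 1.179^(1/5) − 1 = 3.3% per year over 5 years, or 1.179^(1/10) − 1 = 1.7% per year over 10 years. Over 1 year it would need 17.9%.

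**What this could do to a test.** The protocol states no significance rule, so this is only an illustration. If the SMI prevalence were tested against a STEPS value taken as error-free, the chance of a falsely significant excess is Φ[(b − 1.96·SE0)/SE1], where SE0 = √(p0(1 − p0)/1500) and SE1 = √(0.09/1500). The nominal value is 2.5%. The second column allows for sampling error in STEPS with an assumed 1500 respondents.

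| Chance of a false excess, g from 1% to 5% | STEPS fixed | STEPS n = 1500 |
|---|---|---|
| y = 1 | 3-10% | 3-6% |
| y = 5 | 10-85% | 7-55% |
| y = 10 | 26-100% | 14-97% |

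So the artefact can be negligible or can exceed the sampling error, depending on two quantities that cannot be read from the protocol text.

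**The case against.** The strongest reply has four parts.

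- **Survey dates.** One identified survey is cited per country, and the reference list is not in the text available here. The dates may be evident from it. This stands: a reader might infer that the choice of comparator is open, and it is not. Knowing the dates would not, however, remove the period difference.
- **Size.** With a 1-year gap and a 2% annual rise, the false-excess chance against a fixed STEPS value is only about 4-5%. The protocol plans to present and compare prevalences and states no test, so any such probability belongs to an assumed rule. This also stands. The points of drift are the safer measure.
- **Disclosure.** The Discussion admits that there is no control group. It rests comparability on shared questions, shared measurements and a representative survey, so it would be unfair to say that it relies on the questionnaire alone. This is correct, but none of these elements deals with date, and date is not among the limitations.
- **Level of detail.** Sensitivity analyses for an external benchmark are often left to an analysis plan, and this article condenses a fuller document. This stands only in part. The comparator, its aggregate form, the kind of adjustment and the comparability claim are all fixed in the article, and the point follows from these together with the Background's own statement of a rising trend.

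**Conclusion.** The concern holds for non-communicable disease outcomes. As planned, their contrast with STEPS confounds SMI status with calendar time, and the protocol's own premise of rapidly rising rates means that an older comparator could inflate the apparent SMI excess. At 10% prevalence and with no true effect, the artefact is about 0.1 to 3.9 points, against a half-width of 1.5 points. That range rests on an assumed relative rise of 1-5% per year and a gap of 1-10 years.

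Three stronger readings are tempting but not supported:

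- That drift will in fact produce a reported excess. With survey gaps and trends not given, a material effect is possible but not shown.
- That every comparison is biased upwards. The stated trend covers mental illness and non-communicable diseases. For tobacco, alcohol, diet, physical activity, infections and lifestyle advice, the bias could be nil or reversed.
- That differences between countries in the SMI excess become uninterpretable. Ranking countries on that excess is not an objective. What can be said is that such differences could not be separated from differing survey dates, if the dates differ.

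**What to change.** Under Statistical analysis, add a pre-stated sensitivity analysis. Roll each country's STEPS non-communicable disease prevalence forward to the mid-point of data collection over a range of annual changes, taken from successive national surveys where they exist and otherwise from a fixed range. Report that range and the STEPS fieldwork year beside each contrast. Describe an excess as uncertain where it does not hold across the range. A rule that accepts an excess only at the most extreme assumed trend is not needed, and it could hide real differences.

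Under Strengths and limitations, keep the point about shared measures and representativeness, but qualify the comparability claim by naming survey date as a limitation.

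The cost is a few lines of text and one extra table built from published aggregates, with no new data or participants. The downside is that some excesses will be reported less firmly.
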